**Fig. 4 Fig4:**
[figure not shown]
Recruitment and flow. Flow diagram (adapted and modified from the CONSORT statement) demonstrating how the two-step recruitment process and patient flow work. AOK Allgemeine Ortskrankenkasse, CONSORT Consolidated Standards of Reporting Trials, GP general practitioner, HzV Hausarztzentrierte Versorgung

Study participants are allocated as follows. The family doctors inform eligible patients (see Fig. 4 for criteria) about the study and ask their written consent to participate. After consent has been given and the teledermatology process has been completed, the family doctor enters a value in the patient's PMS entry. This value is visible in the subsequent data analysis and identifies the patient as a study participant. Routine data from the general practitioner's practice PMS are then transmitted to the AOK quarterly via a secure data connection. The AOK aggregates the data for the intervention and control circles.

No written consent is required from patients in the control groups. When patients sign an HzV contract with their insurance company, they consent to the anonymized analysis of their insurance data for scientific and quality management purposes.

Candidates in the intervention group practices who do not meet inclusion criteria (e.g., patients insured by other statutory health insurances or not listed as HzV patients) as well as patients refusing the intervention will be treated as usual and referred to a dermatologist. Eligible patients refusing the interventions will be included in an internal control group (see Fig. 4).

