**Methods:**

The TeleDerm study will implement and evaluate store-and-forward teledermatology in 50 general practitioner (GP) practices as an alternative to conventional referrals. TeleDerm aims to confirm that the possibility of store-and-forward teledermatology in GP practices is going to lead to a 15% (*n* = 260) reduction in referrals in the intervention arm. The study uses a cluster-randomized controlled trial design. Randomization is planned for the cluster “county”. The main observational unit is the GP practice. Poisson distribution of referrals is assumed. The evaluation of secondary outcomes like acceptance, enablers and barriers uses a mixed-methods design with questionnaires and interviews.

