**Fig. 2 Fig2:**
[figure not shown]
Project timeline of the 3-year project. GP general practitioner

The cluster level “county” is randomized into four intervention and four control counties. In the intervention counties, data from non-participating HzV practices will serve as an internal control group at the cluster level “practice”. At the cluster level “patient”, data from nonparticipating patients are used as a second internal control group. No blinding is applied to any level of the trial. Figure 3 shows both study arms and an overview of the different cluster levels.

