### Outcomes

The primary outcome measure is the number of conventional referrals from GPs to dermatologists.

Secondary endpoints will be evaluated using a mixed-methods approach. This will allow us to evaluate different aspects of the implementation process. For instance, the teledermatology system will provide information about the referral time and process quality. This data source is complemented by questionnaire surveys from all participating groups. Both care providers (GPs, dermatologists, GP practice staff) and patients (teleconsultation patients and patients who have declined a teleconsultations) will receive questionnaires on acceptance and feasibility. Patient questionnaires will also include all items from the Dermatology Life Quality Index (DLQI) [27]. Semi-structured face-to-face interviews (*n* = 15 patients who have received a teledermatology referral and n = 15 care providers, such as GPs, dermatologists and GP practice staff) will provide additional information to the surveys. Lastly, a health economics analysis based on routine data and support costs for the implementation of the teledermatology system is planned. Study sites (GP practices) will be visited once during the intervention phase by a study nurse for audit.

Details about the outcome parameters are presented in Table 2.

**Table 2 Tab2:** Primary and secondary endpoints, data sources and evaluation methods

Secondary endpoints (intervention group)					Primary endpoint (both groups)
Patients	GPs	Dermatologists	GP team staff	Teledermatology software/KSYOS (process evaluation)	Routine data
Care provider/customer satisfaction, description of technical processes with their advantages and disadvantages				• Number of teleconsultations • Time until dermatologist answers • Number of physical referral recommendations • Number of queries by dermatologists after teleconsultation • Type of disease treated by teleconsultation • Duration of complete teleconsultation process • Result of dermatologic consultation	• Number of referrals to dermatologists by GPs • Ambulatory dermatologic diagnoses • Ambulatory patient contacts with GPs and/or dermatologists due to skin conditions (including EBM^a^ keys) • Number of clinic referrals due to skin conditions
• Quality of life (DLQI, questionnaire) • Satisfaction with dermatologic care/telemedicine (questionnaire, interviews)	Appraisal of feasibility, practicability and barriers for implementation (interviews)				

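### Participant status in the routine data is set only on completion of a teleconsultation, so the patient-level internal control absorbs non-completers and cannot isolate refusers

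*Protocol article*

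**What the plan says.** In Methods, Recruitment and study flow (text after Fig. 4), the capture rule reads: "After consent has been given and the teledermatology process has been completed, the family doctor enters a value" in the patient's record in the practice software. The next sentence gives its role: "This value is visible in the subsequent data analysis and identifies the patient as a study participant". No other patient-level code is described.

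The same subsection says of those who decline: "Eligible patients refusing the interventions will be included in an internal control group". It also says that they "as well as patients refusing the intervention will be treated as usual and referred to a dermatologist".

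The Study design subsection (text after Fig. 2) describes the patient-level comparator more widely: "data from nonparticipating patients are used as a second internal control group". Strengths and limitations gives the internal control group a purpose, the examination of cluster effects.

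Two other places matter. Data analysis says the routine data are anonymized before they reach the institute that analyses them. Outcomes provides for decliners separately: "patients who have declined a teleconsultations) will receive questionnaires on acceptance and feasibility".

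**The concern.** Participation is defined by something that happens after enrolment. A patient can consent, have pictures taken and sent, and still not reach a completed process. Under the printed rule that patient carries no value and is indistinguishable from someone who never took part. The participant group is thereby reduced to the teleconsultations that ran to the end, and the others move to the comparator.

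This is not a neutral loss. The Intervention subsection foresees cases in which the GP's information is insufficient and the dermatologist either advises a physical referral or asks for a second round. The article does not say whether such a case counts as completed. If it does not, the patient and any resulting referral are credited to the control, which favours the intervention in a patient-level comparison.

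Refusers, a clinically distinct group, are also left without any identifier. If the internal control is meant to describe them, the routine data as described cannot do so.

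**Working it through.** The article states no figure for this point, so there is none to reproduce. The first step is to trace who carries the marker.

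| Patient in a participating practice | Consent | Process completed | Marker | Class in routine data |
|---|---|---|---|---|
| Completed teleconsultation | yes | yes | yes | participant |
| Consented, not completed | yes | no | no | nonparticipant |
| Offered, declined | no | no | no | nonparticipant |
| Skin problem, never offered | no | no | no | nonparticipant |
| No skin problem | no | no | no | nonparticipant, but can be filtered out |

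The last row can be removed. Table 2 lists dermatologic diagnoses, skin-related contacts and GP referrals among the routine data. The three rows above it cannot be separated by those fields. A referral does not reveal a refusal, because the Intervention subsection makes use of teledermatology the GP's choice, so a referred, unmarked patient may never have been offered it. Decliner questionnaires show that practices recognise some refusers, but no link from them to the anonymized routine data is described.

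**Illustration of the mix.** From the article (Sample size calculation and Abstract): 120 × 0.40 = 48 referrals per practice-year, and 50 practices × 48 = 2,400 patients with a referral indication. Assumed, not in the documents: offer rate *o* from 30% to 90%, consent *c* from 50% to 90% of those offered, completion *k* from 80% to 95% of consenters. The pool is taken as already restricted to patients with an indication.

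- Marked = 2,400·*o*·*c*·*k*; unmarked = 2,400 − marked
- Refusers = 2,400·*o*·(1 − *c*)
- Consented, not completed = 2,400·*o*·*c*·(1 − *k*)

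Lowest refuser share (*o* = 0.3, *c* = 0.9, *k* = 0.8): marked 518, unmarked 1,882, refusers 72; 72/1,882 = 3.8%.

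Highest refuser share (*o* = 0.9, *c* = 0.5, *k* = 0.95): marked 1,026, unmarked 1,374, refusers 1,080; 1,080/1,374 = 78.6%.

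Fewest misclassed consenters (*o* = 0.3, *c* = 0.5, *k* = 0.95): 18 of 2,058 unmarked, 0.9%.

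Most misclassed consenters (*o* = 0.9, *c* = 0.9, *k* = 0.8): 389 of 845 unmarked, 46%.

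**Effect on the participant side.** Let *r* be the proportion physically referred among completers and *f* that among consenters who do not complete. The proportion among all consenters is *k·r* + (1 − *k*)·*f*. The marked group shows *r*. The gap is (1 − *k*)·(*f* − *r*), which is 0.05 to 0.20 times (*f* − *r*) for the assumed *k*. If non-completers are referred more often, the marked group looks better than all consenters by that amount, and the comparator looks worse as well if *f* exceeds the referral proportion among the other unmarked patients.

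**The case against.** The strongest reply is that this is a journal article. Fig. 4, to which the sentence on refusers points, is not shown, and a list of practice-software codes is the kind of detail left to the full protocol. That limits the claim to the rule as described. It does not remove it, because the rule is stated positively: the value follows completion and identifies the participant.

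A reader might infer several stronger points, which the document does not support.

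- *That a planned acceptance rate loses its denominator.* The Abstract says "The evaluation of secondary outcomes like acceptance, enablers and barriers uses a mixed-methods design" with questionnaires and interviews, and Outcomes repeats this. No proportion of patients offered is planned from routine data. It is true that none of the seven items listed for the teledermatology software counts offers or refusals, but no planned analysis depends on such a count.
- *That the control becomes every unmarked insured patient, most without a skin problem.* The fields in Table 2 allow those patients to be filtered out, so a refuser share computed over whole practice lists is not a fair measure.
- *That the two descriptions of the internal control contradict each other.* Saying that refusers are included in a group does not say that they alone form it. The wider group of nonparticipants can be derived. What is missing is a statement of which group is meant and where non-completers belong.
- *That the main result is at risk.* Data analysis uses study arm with the GP as the unit of observation, and the marker plays no part.

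It also stands that no specified analysis compares refusers, that secondary results are not strictly confirmatory, and that a code for people who declined raises a data-protection question in a setting the Discussion itself calls restrictive.

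**Conclusion.** The point holds in limited form. By the rule as described, consenters who do not complete are counted as nonparticipants and enter the patient-level internal control, and refusers cannot be separated from patients with a skin problem who were never offered teledermatology. Patient-level comparisons with that control contrast completers with a mixed group that includes failed or incomplete teleconsultations.

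The size is unknown from the documents. The ranges (refusers about 4% to 79% of unmarked patients with an indication; 18 to 389 misclassed consenters) rest wholly on assumed offer, consent and completion rates. They show only that the composition cannot be recovered from the marker. The direction of any bias depends on whether non-completers are referred more often, which is plausible from the Intervention text but not stated.

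The primary analysis is unaffected. The change is still worth making, because the internal control has a stated use and offers not recorded during the one-year intervention phase are hard to reconstruct. The article reports that enrolment began in July 2018.

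**What to change.** 1. Enter the practice-record value when teledermatology is offered, with three codes: 'offered, declined', 'consented, not completed' and 'completed'.
2. Count all consenters as participants in patient-level comparisons, whether or not the process was completed.
3. State in both Study design and Recruitment and study flow whether the patient-level internal control is all nonparticipants with a dermatologic diagnosis or referral, or refusers only. Selecting on referral alone would select on the outcome.
4. If a decline code may not be transmitted without consent, at least set the participant code at consent, keep anonymous practice-level tallies of offers and refusals, and do not describe refusers as a separate control group in the routine data.

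The cost is a few seconds of coding per offer, some incomplete coding and a data-protection check for the decline code. Practices must already recognise decliners in order to give them questionnaires, so the added work is small. A proportion consented out of those offered would then become available as an added benefit.

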### Sample size calculation

The main scientific hypothesis is that the possibility of teledermatology in general practice will reduce the number of referrals to a dermatologist by 15% in the intervention group. The statistical null hypothesis is a reduction of 0%, the alternative is a reduction > 0%. The basis of the sample size calculation is an assumed reduction of 15%.

A mean of 120 referrals to dermatologists per year and GP is assumed. In 2015, 40% of AOK-insured patients were enrolled in the HzV [28, 29]. Thus, for the subgroup of AOK patients, 48 dermatological referrals per year and GP practice are to be expected in the control population during the 1-year intervention phase of the study. A Poisson distribution of the referrals for each GP team is assumed. Furthermore, a type I error of 5% (two-sided) and a type II error of 20% are defined. These assumptions lead to a calculation of 36 analyzable GP teams (with, on average, 48 referrals per year and GP practice each) per study arm. On the patient level, this amounts to 1728 patients with the indication for a referral to a dermatologist in total. A 15% reduction equals 260 referrals in total. A 30% dropout buffer is taken into account. The final sample size calculation amounts to 2400 patients with a reduction of 360 referrals.

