### Data analysis (t_2_ in Fig. 1)

The pooled routine dataset is sent from AOK to the aQua institute. The aQua institute selects, filters and anonymizes the data. Lastly, the aQua institute delivers the anonymized patient dataset to the Institute for Clinical Epidemiology and Applied Biometry (IKEaB) for statistical analysis. All of these transfers use a secure, encrypted protocol and are authenticated. The relevant data sources are subject to extensive quality management processes. To secure data protection of interview and questionnaire data as well as process data from the KSYOS system, the Tübingen University Hospital’s (UKT) data protection agency is involved. They are independent from the sponsor.

For the primary outcome, Poisson regression is chosen as an analysis tool. To consider practice size and patient load, the number of practice KV bills during the intervention phase is applied as an offset. The dichotomous factor “study arm” is applied for the calculation. The GPs are the unit of observation. For both study arms, separate confidence intervals are created for the number of referrals per KV bill.

For the sample size calculation, a simple *t* test was used. In contrast to the sample size calculation, the statistical analysis will use a more complex method (Poisson regression). This is expected to lead to an increased power of the study, because the offset “total number of KV bills during intervention” explains parts of the variability between GP teams. Study power should thus be over 80%. Primary analysis will be calculated as a Poisson regression with a significance level of 5% (two-sided). Analogous methods will be applied to secondary outcomes (see later). However, the interpretation of local significances is not designed to be strictly confirmatory. Due to the multitude of secondary parameters lacking hierarchical structure, a correction for multiple tests is unrealistic. Descriptive analyses are performed following scaling and observed data distribution.

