Another challenge for the implementation of telemedicine in German primary care is the heterogeneity of practices. Basically each aspect of daily work (team structure, patient management software, size of the practice, practice organization) is different between practices [33]. For example, about 235 different digital patient data management systems exist in Germany [34]. In 2017, German law enforced the implementation of a generic patient data interface within 2 years [35]. Using such an interface is currently the only way to export patient data to third-party solutions, like the KSYOS teledermatology system. Nevertheless, there still are some PMSs that do not support such an interface or ask for licensing and support fees. The GP may use the teledermatology nevertheless by manually importing and exporting data, but that might prove too time-consuming for daily practice. The consequence might be that the GP drops out of the study.

To ensure the intervention’s success, GPs must be allowed to choose their own way of implementing the intervention in their practice. Thus, it is allowed for GPs to delegate parts of the teledermatology procedure (e.g., photography of the skin lesions) to practice staff. This way, the acceptance of the intervention hopefully increases, thus resulting in more realistic and reliable results.

In order to grasp the multitude of different perspectives, a mixed-methods evaluation was designed. We hope to identify relevant barriers and enablers for the implementation of sustainable teledermatology in routine general practice. If we succeed, the TeleDerm study could be a milestone in the implementation of telemedicine in general and teledermatology in particular in Germany.

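### The primary Poisson regression has no term for practice-to-practice variation beyond the offset, so the 5% test is anti-conservative wherever such variation remains

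*Protocol article*

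**What the plan says.** **Sample size calculation (Protocol article).** The control rate starts from "A mean of 120 referrals to dermatologists per year and GP is assumed". Taking 40% of it, "48 dermatological referrals per year and GP practice are to be expected in the control population". The distribution is stated as "A Poisson distribution of the referrals for each GP team is assumed", and the abstract repeats "Poisson distribution of referrals is assumed". The target is a 15% reduction, and "a type I error of 5% (two-sided) and a type II error of 20% are defined". The result is 36 analysable practices per arm. No SD or between-practice variance is given.

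**Data analysis.** The calculation is said to have used a simple t test. The confirmatory analysis is a two-sided 5% Poisson regression with the GP as unit of observation, study arm as the factor and the number of KV bills as offset. Separate confidence intervals for referrals per KV bill are planned for each arm. The offset is expected to raise power because it "explains parts of the variability between GP teams". The section names no dispersion parameter, negative binomial model, robust variance or practice random effect.

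**Discussion.** "Another challenge for the implementation of telemedicine in German primary care is the heterogeneity of practices". Under Strengths and limitations, this heterogeneity is expected to affect GPs' referring activity, and the stated response is to recruit 30% more GPs.

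**The concern.** With study arm and an offset as its only terms, a Poisson regression treats all practices in an arm as having one true referral rate per KV bill. Any real difference in that rate between practices makes the counts more variable than the model allows. The model-based standard error is then too small by the square root of the dispersion factor.

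Having a single count per practice does not prevent this, because overdispersion is a property of the spread between practices and not of repeated measurement. Recruiting 30% more practices does not cure it either: more practices add precision, but the standard error stays understated by the same factor.

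At stake are the confirmatory p-value and the per-arm confidence intervals. The problem is separate from county clustering and comes on top of it. Adding only a county term to a practice-level Poisson model would leave the variation among practices within a county unmodelled.

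**Working it through.** **Inputs from the protocol.** Control mean 120 × 0.40 = 48 per practice-year; intervention mean 48 × 0.85 = 40.8; difference 7.2; two-sided alpha 0.05; power 0.80; stated result 36 per arm. Under Poisson variance the SD is √48 = 6.93.

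**Step 1: the plan's own figure.** n per arm = 2 × SD² × (1.960 + 0.842)² / difference² = 2 × 48 × 7.85 / 51.84 = 14.5, so 15. An exact t-test calculation gives 16. The stated 36 is not reproduced; with Poisson variance, 36 per arm would have about 99% power.

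**Step 2: the SD that 36 would imply.** SD = 7.2 / (2.802 × √(2/36)) = 10.9 by the normal formula and 10.75 by the t test. The second gives variance/mean = 115.6 / 48 = 2.41. This SD is back-calculated. Pairing √120 = 10.95 with the difference of 7.2 gives 36.3, nearly the stated number, so a mix of the 120 and 48 scales is another possible origin. The document settles neither.

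**Step 3: type I error of the plain Poisson test.** If true practice rates vary with coefficient of variation CV after the offset, the variance is mean + mean² × CV². The dispersion factor at a mean of 48 is therefore φ = 1 + 48 × CV². The standard error is understated by √φ, and the true two-sided error is 2 × (1 − Φ(1.96/√φ)). CV is an assumption.

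| Residual CV (assumed) | φ | SE too small by factor | Type I error (formula) | Simulation, 36 per arm |
|---|---|---|---|---|
| 0 | 1.00 | 1.00 | 5.0% | 4.9% |
| 0.1 | 1.48 | 1.22 | 10.7% | not run |
| 0.2 | 2.92 | 1.71 | 25.1% | 24.5% |
| 0.3 | 5.32 | 2.31 | 39.5% | 39.0% |

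The simulation drew gamma-Poisson counts for independent practices, with no county effect. In the same runs a practice-level robust standard error held the error between 4.8% and 4.9%.

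**Step 4: the scenario behind 36.** Suppose the SD of 10.75 is genuine between-practice spread.
- Offset removes none of the excess: φ = 2.41, √φ = 1.55, type I error 21%.
- Offset removes half: φ = 1 + 1.41/2 = 1.70, type I error about 13%.
- Offset removes all: φ = 1, type I error 5%.

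**Step 5: what a corrected test costs in power.** On the log rate-ratio scale, 13.5 × φ practices per arm are needed for 80% power. With 36 per arm, a dispersion-corrected test has power of about 90% at φ = 2, 82% at 2.5 and 75% at 3. It falls below 80% above about φ = 36/13.5 = 2.7. This too is before any county effect.

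**The case against.** The strongest reply is that an article naming the model family, factor, offset and alpha has not said that the scale is fixed at 1; the variance estimator may be settled in an analysis plan that is not shown. That is fair as far as it goes. But the article states the distribution and the model for the confirmatory test and builds a power argument on it, so naming a model that allows for dispersion improves what is written and does more than fill in detail.

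Other points also carry weight:
- The sentence on the Poisson distribution is a sample-size assumption, and Poisson for each team could mean Poisson within a team with rates that differ between teams. The case therefore rests on the primary model in Data analysis.
- The offset remark does not prove residual overdispersion. Variability between raw counts includes Poisson noise, so an offset that removed all extra-Poisson variation would still explain only part of the total.
- Much of the heterogeneity described concerns software, organisation and uptake. The link to referral counts rests mainly on one unquantified sentence in Strengths and limitations.
- The statement that GP-level analyses need no cluster adjustment stands in the paragraph on secondary outcomes. It names AOK insurance data, the primary data source, but is supporting evidence at most.

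Three stronger readings are tempting and not supported. A reader might infer that the standard errors are certainly understated; the document gives no residual dispersion, and at φ = 1 there is no understatement. A reader might take 21% as the expected type I error; it is the ceiling of one scenario, resting on a back-calculated SD and an offset that removes none of the excess. A reader might conclude that the claimed power gain from the offset is wrong; relative to an unadjusted t test, an offset that explains between-team variability does raise power, so that statement can stand.

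**Conclusion.** The point holds in conditional form. As written, the primary analysis gives an anti-conservative test and per-arm intervals that are too narrow wherever practices still differ in their referral rate per KV bill. The document gives reason to expect some such difference but does not quantify it.

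The effect is not small even for modest heterogeneity: an assumed residual CV of 0.1 already roughly doubles the nominal error, and 0.3 takes it to about 40%. These figures assume a mean of 48, independent practices and no county effect.

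The 36 per arm does not follow from Poisson variance. It leaves room for dispersion of about 2.4 to 2.7, so the sharper problem lies in the validity of the planned test and less in the number of practices.

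**What to change.** - Keep the KV-bill offset. Specify the practice-level primary model as negative binomial regression, or as Poisson with a practice-level random effect or a dispersion-robust standard error. Use the same variance for the per-arm confidence intervals.
- Do this in addition to handling county clustering; a practice-level correction alone does not cover counties. A county-level two-stage analysis would cover both.
- State the SD and its source behind the 36 practices per arm.

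The cost is wording, settled before the data are analysed. Intervals will be wider if overdispersion exists, which is then the correct width; if it does not, almost nothing is lost.
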